### Data collection and measurements

CCS who transition regularly from pediatric care, will be informed about interdisciplinary LTFU care by their treating pediatric oncologist. This information is communicated up to one year before the transition to allow the CCS to adapt to the upcoming change. A few weeks before the first LTFU consultation, the CCS will be informed about the LE-Na study according to local standards, e.g. via telephone plus additional information via e-mail.

CCS registered in the GCCR receive a letter with study information as well as a list of all LTFU clinics which are part of the LE-Na project. When interested, they contact a clinic nearby, may ask questions about LTFU and arrange a date for the consultation.

CCS who become aware of the study through the media contact the center of their choice directly, have the opportunity to receive further information and arrange an appointment (see Fig. 2).

**Fig. 2 Fig2:**
[figure not shown]
Recruitment strategies for the LE-Na study

On the day of the consultation, CCS will first be welcomed by the LTFU team and receive information about the study from a designated team member, e.g. the study coordinator or psychologist. If participation in the study is desired, patients sign the consent form and receive a tablet on which they fill out the study questionnaires and those of the psychosocial screening. The completion duration is around 20–30 min. This is followed by a consultation with the LTFU care doctor and all the necessary examinations (e.g., ECG, MRI), which were planned beforehand based on the previous oncological disease and treatment exposure (risk stratification [6], see “Standardized LTFU care and risk stratification” below). If examinations are not available at some centers, patients are advised how to coordinate a separate appointment. In these cases, the corresponding LTFU care center collects these additional data and documents them in the database afterwards. Thereafter, the patient is introduced to the psychosocial expert, who explores the psychosocial history based on the psychosocial screening and identifies any psychosocial difficulties (see “ Psychosocial screening” below). After case discussion in the interdisciplinary team, the results of the examinations and expected long-term consequences are communicated with the patient, who thereby receives an individualized LTFU plan. After the consultation, all examination results and the patient's medical history are documented in a CTMS; the completed questionnaires (both for evaluation and for psychosocial screening) are transferred automatically to the CTMS (see “ Data processing and data quality” below).

The waiting control group (study phase 2) receives the standard care provided by their general practitioner during a one-year waiting period. The extent of this individual use of preventive examinations before participation in the study is assessed in the studies questionnaire.

The instruments to assess the study outcomes are summarized in Table 1.

In addition to measuring the displayed outcomes, several secondary analyses will be carried out:Gender differences in study recruitment strategies – It will be investigated whether different recruitment strategies result in differences in the gender distribution among study participants. Therefore, the study centers document in the CTMS how each participant became aware of the study: Either through transition, the GCCR or media.Sensitivity of the questionnaire-based psychosocial screening compared to the interview-based psychosocial anamnesis – This will be operationalized as the number of cases that receive a psychosocial follow-up appointment due to the interview-based psychosocial history, although the cut-off values of the questionnaire-based psychosocial screening were not exceeded.An interim analysis after one study year is going to be performed to identify problems in study recruitment (with regard to the three different recruitment strategies) as well as possible underrepresentation of certain survivor groups (for example survivors with migration background). For this analysis, all survivors that do not meet the inclusion criteria or meet one exclusion criterion are documented in each center anonymously (age, gender, primary cancer, exclusion / inclusion criterion (not) met). Also, a non-responder analysis of those survivors that are contacted via the German childhood cancer registry is going to be conducted. Adaptations in recruitment strategies in order to engage study participation are going to be discussed based on this interim analysis.

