### Psychosocial screening

Psychosocial screening questionnaires are presented via tablet following those questionnaires to assess primary and secondary outcomes. They focus on (mental) health impairments which have been identified as relevant for survivors after childhood cancer [9, 10] and includes widely established questionnaires which have been implemented in former prevention studies recruiting childhood cancer survivors in Germany ( [11] see Table 2). In order to adapt the screening procedure for survivors with cognitive impairments, a short version is offered including the Distress Thermometer without additional questions on daily life issues, the PHQ-4 and a single question on posttraumatic symptoms. First, all CCS start with the same questionnaires and are asked to complete the long form, if possible. However, if they feel tired or exhausted, they can choose to switch to the short form after filling out the FA 12 (see Table 2). This approach is going to be evaluated in an interim analysis after one year. Psychosocial experts are able to retrieve an individual summary of results with guidance on interpretation and cut-off via CTMS. They are encouraged to include screening results into the psychosocial anamnesis, focusing on those symptom areas patients indicated score above the cut-off. This is especially relevant in those patients who completed the short form of the screening or who indicated suicidal ideation in the PHQ-9 in the long form. For the same reason LTFU teams are advised not to offer the psychosocial screening if psychosocial experts or physicians experienced with mental health impairments are not available during the consultation day and cannot follow- up the screening results face-to-face. In order to provide a harmonized approach and improve quality assurance regarding the psychosocial screening, psychosocial experts are invited to participate in regular intervision meetings.

**Table 2 Tab2:** Questionnaires used in the psychosocial screening in LE-Na

Long Form Psychosocial Screening	Short Form Psychosocial Screening
EORTC QLQ C30 [12]	EORTC QLQ C30 [12]
EORTC QLQ FA12 [13]	EORTC QLQ FA12 [13]
Distress Thermometer with problem areas [14]	Distress Thermometer without problem areas [14]
PHQ-4 [15]	PHQ-4 [15]
PHQ-9 (last seven questions) [16]	
IES-R [17]	Screening question PTSD [9]
Questions on life situation and educational & occupational outcomes	Questions on life situation and educational & occupational outcomes

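### The psychosocial screening's sensitivity is defined as a count of missed cases, which has no denominator and does not determine a sensitivity

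*Protocol article*

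**What the plan says.** The list of secondary analyses at the end of Data collection and measurements names the target quantity: "Sensitivity of the questionnaire-based psychosocial screening compared to the interview-based psychosocial anamnesis". The questionnaire is therefore the test under study and the interview is the reference.

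The same item then states how this will be measured. "This will be operationalized as the number of cases that receive a psychosocial follow-up appointment due to the interview-based psychosocial history", with the further condition "although the cut-off values of the questionnaire-based psychosocial screening were not exceeded".

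Two other places describe how the interview is done. Data collection and measurements says that the patient meets the psychosocial expert after the tablet questionnaires, "who explores the psychosocial history based on the psychosocial screening and identifies any psychosocial difficulties". The section Psychosocial screening adds: "Psychosocial experts are able to retrieve an individual summary of results with guidance on interpretation and cut-off via CTMS". It continues: "They are encouraged to include screening results into the psychosocial anamnesis, focusing on those symptom areas patients indicated score above the cut-off". The article describes no blinded or independent interview for this analysis.

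It gives no expected sensitivity, precision target or sample size for the item.

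**The concern.** Sensitivity is a proportion: of all people with the condition according to the reference, the share whom the test flags. The definition in the article keeps only those whom the test did not flag, and it asks for their number rather than their share. The people whom the screening caught do not appear in it, and neither does the total with an interview-identified need.

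Followed as written, the analysis would yield a figure that cannot be read as a sensitivity or compared with one. It could not be compared across centres or periods that screened different numbers of people. A reader who took a small count as evidence of a good screening could be looking at a small sample or a population with few cases.

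A second, lesser issue is the reference itself. The interviewer knows the screening result, so the two assessments are not independent.

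**Working it through.** There is no figure in the article to reproduce. The check is one of definition, followed by illustrations with assumed counts.

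**Step 1: what is counted.** Cross-classify participants by interview (follow-up needed or not) and screening (a cut-off exceeded or not):

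| | Interview: follow-up | Interview: no follow-up |
|---|---|---|
| Cut-off exceeded | TP | FP |
| No cut-off exceeded | FN | TN |

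Sensitivity = TP/(TP + FN). The article's measure requires follow-up because of the interview and no cut-off exceeded. That is the FN cell alone.

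**Step 2: the same count fits very different sensitivities.** Hold FN at 20 (assumed) and vary TP:

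| TP | TP/(TP + 20) | Sensitivity |
|---|---|---|
| 20 | 20/40 | 50% |
| 80 | 80/100 | 80% |
| 180 | 180/200 | 90% |
| 380 | 380/400 | 95% |

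**Step 3: the same sensitivity gives very different counts.** Hold sensitivity at 80%. Then FN = number screened × share with a need × (1 − 0.80). The article aims for 5000 participants overall and assumes 1000 included per year. The shares with a need, 10% and 30%, are assumptions.

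| Screened | Share with need | Calculation | FN |
|---|---|---|---|
| 1000 | 10% | 1000 × 0.10 × 0.20 | 20 |
| 1000 | 30% | 1000 × 0.30 × 0.20 | 60 |
| 5000 | 10% | 5000 × 0.10 × 0.20 | 100 |
| 5000 | 30% | 5000 × 0.30 × 0.20 | 300 |

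The count varies fifteen-fold (300/20) with no change in how well the screening works.

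**Step 4: what an unblinded interview could do.** Assume a true TP of 160 and a true FN of 40, so a sensitivity of 160/200 = 80%. Suppose that the interview finds every screen-positive case but only part of the screen-negative ones:

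| Share of screen-negative cases found | Count of missed cases | Apparent sensitivity |
|---|---|---|
| 100% | 40 | 160/200 = 80% |
| 75% | 30 | 160/190 = 84% |
| 50% | 20 | 160/180 = 89% |
| 25% | 10 | 160/170 = 94% |

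This shows a direction and a possible scale only. Nothing in the article says how large the loss would be, or that there is one.

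**The case against.** **An article leaves such details to the analysis plan.** This would be a good answer had the article merely named the sensitivity and stopped. It goes on to say how the quantity is operationalized, and that statement does not match the name. The deferral to the analysis plan stands in the Statistical analysis section, in the paragraph on the primary analyses, and does not correct a definition already given.

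**The count answers a legitimate, narrower question.** It does show how many people the interview picked up although their questionnaire was unremarkable. That stands, and it is why renaming the measure is an acceptable repair. It is not what the item is called.

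**The steering of the interview can be overstated.** A reader might infer that interviewers pursue areas above the cut-off, overlook the rest, and so make the sensitivity demonstrably too high. The documents do not support that much. The counted people are those with no cut-off exceeded. Read at the level of the person, they have no flagged area to which attention could be drawn. The use of results is encouraged, not required. What remains is that an expert who has seen an unremarkable summary may probe less. That is plausible, but of unknown size. Showing the results to the expert is also a reasonable care procedure. The limitation concerns only its use as a reference.

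**A reader might infer that the aim is to let the questionnaire replace or trigger the interview.** The article does not say so. It sends the patient to the psychosocial expert without making a cut-off a condition, and it advises against offering the screening when nobody qualified can follow up face to face.

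**A reader might object to pooling the long and short forms.** Participants may change form ("they can choose to switch to the short form after filling out the FA 12"), and Table 2 shows that the instruments differ in part. But reporting by form is ordinary analysis-plan detail, and the article already plans to evaluate the two-form approach after one year. This is no defect.

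**Conclusion.** The point holds in a limited form. The measure is the false-negative count. It moves in the opposite direction to sensitivity, grows with the number screened, and does not determine sensitivity. In the illustration, 20 missed cases are compatible with anything from 50% to 95%. This follows from the definition. Only the sizes rest on assumed counts.

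The interview is not independent of the screening. The likely direction is in favour of the screening and the amount is unknown. This calls for a stated limitation, not a claim of proven bias.

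The item is one of several secondary analyses outside the outcomes in Table 1. It touches neither the primary endpoints nor the sample size. It should be corrected because the announced quantity cannot be obtained as defined and the correction is cheap.

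**What to change.** 1. Define a case as a participant in whom the interview identifies a need for psychosocial follow-up, whatever the screening result. Keep the attribution to the interview. Counting every appointment made afterwards would let a high questionnaire score prompt the appointment and so create its own true positive.
2. Report sensitivity = cases with at least one cut-off exceeded/all cases, with a 95% confidence interval. The number of missed cases can be shown beside it.
3. Confirm that the appointment and its reason are recorded for screen-positive participants too. The article says that questionnaires, examination results and medical history go into the database, but it does not state this item.
4. If it is not recorded and cannot be added, drop the word sensitivity. Report instead the proportion of screen-negative participants with an interview-identified need, FN/(FN + TN), with a 95% confidence interval. This has a proper denominator, but it depends on how common the need is and must not be read as a sensitivity.
5. In either case, state that the interviewer sees the screening result, so the reference is not independent and the estimate probably favours the screening by an unknown amount.

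The cost is a change of wording, slightly more analysis work and possibly one additional recorded item. The care procedure need not change.

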### Standardized LTFU care and risk stratification

Standardized LTFU care is performed by an interdisciplinary team consisting of a core team (specialists for pediatric oncology and internal medicine, psychosocial expert and a case manager) and further organ specialists (e.g. neurologists, dermatologists). It is based on a compilation of international evidence-based guidelines from the International Guideline Harmonisation Group (IGHG) and PanCare that have been summarized in 2020 and updated in 2023 [3, 6]. This compilation includes examinations for early detection of possible late effects primarily aiming at asymptomatic survivors. All participating clinics have experience with LTFU for CCS and have all necessary resources to perform standardized LTFU care which was independently reviewed prior to the study initiation by an external advisory board consisting of 4 survivorship specialists from Germany, Austria and Switzerland.

During LTFU, a previously published definition of three different risk groups based on cancer treatment exposure is used to stratify CCS according to their future risk to develop late effects [6, 8]. In this risk stratification, risk group 1 (RG1) includes CCS with a low risk for late effects. This group comprises CCS who were treated with surgical therapy (except CCS with a central nervous system (CNS) tumor), survivors of acute lymphoblastic leukemia and patients with non-hereditary retinoblastoma who received chemotherapy only. Risk group 2 (RG 2) includes CCS with an intermediate risk for late effects, such as survivors following chemotherapy only (excluding CCS assigned to RG1) or survivors of CNS tumor who had undergone surgical therapy. CCS with the highest risk for late effects are summarized in risk group 3 (RG3) such as survivors after hematopoietic stem cell transplantation and/or radiotherapy [5]. CCS return periodically to the clinic depending on their RG (RG 1: every 5 years, RG 2: every 2 to 3 years, RG 3: yearly) and continuously receive LTFU care.

### Psychosocial screening

Psychosocial screening questionnaires are presented via tablet following those questionnaires to assess primary and secondary outcomes. They focus on (mental) health impairments which have been identified as relevant for survivors after childhood cancer [9, 10] and includes widely established questionnaires which have been implemented in former prevention studies recruiting childhood cancer survivors in Germany ( [11] see Table 2). In order to adapt the screening procedure for survivors with cognitive impairments, a short version is offered including the Distress Thermometer without additional questions on daily life issues, the PHQ-4 and a single question on posttraumatic symptoms. First, all CCS start with the same questionnaires and are asked to complete the long form, if possible. However, if they feel tired or exhausted, they can choose to switch to the short form after filling out the FA 12 (see Table 2). This approach is going to be evaluated in an interim analysis after one year. Psychosocial experts are able to retrieve an individual summary of results with guidance on interpretation and cut-off via CTMS. They are encouraged to include screening results into the psychosocial anamnesis, focusing on those symptom areas patients indicated score above the cut-off. This is especially relevant in those patients who completed the short form of the screening or who indicated suicidal ideation in the PHQ-9 in the long form. For the same reason LTFU teams are advised not to offer the psychosocial screening if psychosocial experts or physicians experienced with mental health impairments are not available during the consultation day and cannot follow- up the screening results face-to-face. In order to provide a harmonized approach and improve quality assurance regarding the psychosocial screening, psychosocial experts are invited to participate in regular intervision meetings.

**Table 2 Tab2:** Questionnaires used in the psychosocial screening in LE-Na

Long Form Psychosocial Screening	Short Form Psychosocial Screening
EORTC QLQ C30 [12]	EORTC QLQ C30 [12]
EORTC QLQ FA12 [13]	EORTC QLQ FA12 [13]
Distress Thermometer with problem areas [14]	Distress Thermometer without problem areas [14]
PHQ-4 [15]	PHQ-4 [15]
PHQ-9 (last seven questions) [16]	
IES-R [17]	Screening question PTSD [9]
Questions on life situation and educational & occupational outcomes	Questions on life situation and educational & occupational outcomes

### Data processing and data quality

All examination results and the patient's medical history are documented in a CTMS after the patient's consent has been obtained [5]. The documentation takes place every time the patient attends the clinic during the study period (e.g. yearly for CCS assigned to RG 3, see also “standardized LTFU care and risk stratification”) although information on primary cancer diagnosis and treatment are only filled out at first data entry. This enables a central and uniform recording of chronic health conditions in CCS and facilitates the subsequent evaluation of the study. Each center has its own area to document the subjects pseudonymously. In total, the study consists of 15 case report forms (CRFs). 10 CRFs are filled out by the subjects themselves using a tablet (for further information about the database, see [5]). Depending on the risk group and the respective study phase, the corresponding CRFs are displayed on the tablets and completed by the study participant. The completed CRFs are then transferred to the CTMS. The study coordinator ensures that the assignment was carried out correctly. Data management includes more than 50 validation rules and further plausibility checks. Intermediate evaluations are planned to monitor data quality.

### Statistical analysis

With regard to the pre-post-comparison after three years in phase 1, small to medium effect sizes can be assumed based on the literature. However, it must be considered that the largest effects are expected in the stratum (i.e. in the group) of patients with high and medium risk, and smaller effects in the stratum of patients with low risk. Therefore, the two strata with high and medium risk are first tested equally, and the stratum with low risk is tested separately in a hierarchical manner. In order to comply with the global significance level of 5% when testing initially two strata and two primary endpoints, a local significance level of 1.25% is used in each case. With a power of 90%, a sample of *n* = 370 per stratum is sufficient to detect an effect of delta = 0.2. This number is achieved in the strata with medium and high risk if 1000 patients are included per year, of whom 400 patients fall into the group with high and medium risk respectively and of whom about 95% participate in the study. Patients enrolled in the first year will be surveyed in the fourth year with a 3-year follow-up, at which time the primary outcome criteria will be measured.

Regarding the parallel group comparison in phase 2, the sample size is estimated so that an effect of delta = 0.25 can be detected with a power of 80% for both primary endpoints. 310 patients per risk group (each in the intervention and control group), i.e. 620 patients in one stratum, must therefore be included in the study. If the participation rates in the first two years of the study (captured in an interim evaluation after two years) already indicate that the number of probands for the summative evaluation will be too low despite the recruitment measures described, only one single endpoint can be analyzed in the final evaluation. In this case, 255 patients per group in one stratum, i.e. 510 patients in one stratum in total, would be included in the study.

In both phases, the primary analyses will be performed by estimating generalized linear models including primary oncological disease, sex, and time since treatment as covariables. Details will be fixed in the statistical analysis plan.

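### Phase 1 holds all four initial primary tests at a fixed 1.25%; this is valid, but Holm's step-down over the same four tests gains power at the same 5% familywise error

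*Protocol article*

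**What the plan says.** Protocol article, Statistical analysis, phase 1. The order of testing is that "the two strata with high and medium risk are first tested equally, and the stratum with low risk is tested separately in a hierarchical manner". The overall level is 5%, and to hold it over these four comparisons the article says that "a local significance level of 1.25% is used in each case". That is 5%/4, and no step-down or passing on of unused alpha is described. The sample size follows from this level; for 90% power per test, the article states that "370 per stratum is sufficient to detect an effect of delta = 0.2". It does not say which results open the low-risk tests.

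Phase 2, same section. The size of 310 per group is chosen so that an effect of 0.25 "can be detected with a power of 80% for both primary endpoints". No local significance level is given. If recruitment is low, the plan falls back to a single endpoint with 255 per group. The section leaves analysis details to the statistical analysis plan, which is not shown.

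**The concern.** Four tests at a constant 1.25% use the 5% only in the least favourable case. Once one hypothesis is rejected, at most three can still be true nulls, so the remaining tests could be run at a higher level without exceeding 5% overall. Holm's procedure does this with no extra assumption about the correlation between endpoints, no ordering of hypotheses and no extra patients. Keeping 1.25% throughout therefore gives up power in the initial tests.

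The plan has little slack. The expected first-year intake per stratum is 400 × 0.95 = 380, so 370 evaluable leaves room for a loss of only 10/380 = 2.6% over three years. The low-risk stratum is also tested after the other two, so the results of the initial tests may decide whether it is reached.

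**Working it through.** **Inputs from the Statistical analysis section.** Familywise 5%; 2 strata × 2 endpoints = 4 tests; 1.25% each; power 90%; effect 0.2, taken as standard-deviation units of the pre-post change; n = 370 per stratum. **Assumed:** two-sided tests, independent strata, and a correlation rho between the two endpoints within a stratum. The article gives no correlation, so 0 to 0.7 was tried.

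**1. The plan's own figure.** For a paired test on the change, n = ((z(0.99375) + z(0.90))/0.2)² = ((2.498 + 1.282)/0.2)² = 357.1, so 358. The noncentral t gives 361. At n = 370 the noncentrality is 0.2 × √370 = 3.847, and power is Φ(3.847 − 2.498) = 91.1%. The stated 370 therefore fits a two-sided 1.25% level; a one-sided 1.25% level would need only 311 to 313.

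**2. The two procedures.** Bonferroni compares every p-value with 1.25%. Holm compares the ordered p-values with 5%/4 = 1.25%, 5%/3 = 1.67%, 5%/2 = 2.5% and 5%, stopping at the first failure. Simulation with 1,000,000 replicates, effect 0.2 in all four tests:

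| n | rho | Per test, Bonferroni | Per test, Holm | All four, Bonferroni | All four, Holm |
|---|---|---|---|---|---|
| 370 | 0 | 91% | 96.6% | 69% | 88% |
| 370 | 0.3 | 91% | 96.5% | 71% | 89% |
| 370 | 0.5 | 91% | 96.3% | 72% | 89% |
| 370 | 0.7 | 91% | 96.0% | 74% | 90% |
| 300 (assumed loss) | 0.3 | 83% | 91.5% | 51% | 76% |

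The chance of at least one rejection is the same for both methods (99.97% at n = 370, rho 0.3), because both start at 1.25%.

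**3. Familywise error.** With all four nulls true, it is 4.9% for both methods at rho 0. Across the mixed configurations tried, Holm gave 4.4% to 5.0%.

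**4. Other effect patterns (n = 370, rho 0.3).**
- Effect 0.2 on one endpoint, none on the other: power per test on the active endpoint goes from 91% to about 93%.
- Effects 0.2 and 0.1: 91% to about 93.5% on the stronger endpoint; all four, 7% to 21%.
- Effect 0.3 everywhere: all four, 99.8% to almost 100%, so practically no gain.

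**5. The low-risk gate.** With effect 0.2 everywhere, Holm opens an all-four gate with probability 89%. Suppose instead that the plan intends a hierarchy within each endpoint, opened when both higher-risk strata succeed on that endpoint. Fixed 1.25% tests then open at least one low-risk test with probability 95.5%. If one endpoint has no effect, the figures are about 0.2% for the all-four gate under Holm and 83% for the per-endpoint gate.

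**6. Phase 2.** Two-sample comparison, effect 0.25, power 80%. At 2.5%, n = 2 × ((2.241 + 0.842)/0.25)² = 304 per group, close to 310. At 5%, n = 2 × ((1.960 + 0.842)/0.25)² = 251, close to 255. The two sizes are thus consistent with an equal split over two endpoints and with a single test. If that is the rule, the noncentrality at 310 per group is 0.25 × √155 = 3.11. Power per endpoint is then about 81% with a fixed 2.5% and about 86% with Holm (rho 0.3); both significant, 68% against 78%.

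**The case against.** **The plan is not wrong.** This stands. Bonferroni at 5%/4 keeps the promised 5%, and 370 per stratum gives the planned power. A reader might infer an error or an underpowered trial; the article supports neither.

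**All four succeeding is not the plan's criterion.** This also stands. Nothing in the article requires four rejections for a positive result, so a rise from 71% to 89% should not be read as a rise in the chance of trial success. The per-test gain is the fairer measure.

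**The gain depends on the effects.** This stands too: the article expects small to medium effects, and the benefit shrinks when they are larger or differ between endpoints.

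**The article may only be sizing the trial at 1.25%, with a step-down left to the analysis plan.** This is possible, since Holm's first threshold is also 1.25%. But the level is stated as the one used in each case, which reads most naturally as fixed, so the point is fair to raise on the text as it stands.

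**Holm may not be free for the whole procedure.** This matters. A reader might infer that confidence intervals are the only cost. However, the article says only that "the stratum with low risk is tested separately in a hierarchical manner", not what opens those tests. Alpha recycled among the first four cannot also be handed to the low-risk stratum, and an all-four gate can be harder to open than a per-endpoint one. That Holm never rejects less is true of the four initial tests, not necessarily of the whole sequence.

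**Phase 2 states no local level.** Correct. A fixed 2.5% is an inference from 310 per group, so the phase 2 part is conditional.

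**Conclusion.** The point holds as an inexpensive efficiency gain, not as a correction of an error. If the true effect is 0.2 in all four tests and 370 per stratum are evaluable, Holm raises power per test by about 5 percentage points (91% to 96.5%). With an assumed 300 evaluable the gain is about 8 points (83% to 91.5%), so the change also offers some protection against loss to follow-up. These figures rest on an assumed endpoint correlation of 0.3; values from 0 to 0.7 change them little. The effect assumption matters more: the gain falls to 1 to 2 points on the active endpoint if the other has no effect, and almost vanishes at 0.3. The chance of at least one significant result is unaffected. How the change bears on the low-risk stratum cannot be settled from the article, because the gate is not defined there.

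**What to change.** Before primary outcome data are analysed, replace the fixed 1.25% by Holm over the four initial tests (1.25%, 1.67%, 2.5% and 5% on the ordered p-values) and keep n = 370 per stratum.

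In the same place, state what opens the low-risk tests. There are two sound options:
- Open them with the full 5%, itself shared over the two endpoints by Holm, only after all four initial rejections.
- If a hierarchy within each endpoint is intended, prespecify a graphical Bonferroni-based procedure that shows how alpha moves between the initial and the low-risk tests.

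For phase 2, state the multiplicity rule. If it is an equal split, use Holm (2.5%, then 5%). Under that assumption, at the fallback size of 255 per group Holm gives about 78% power per endpoint with both kept, against 72% with a fixed 2.5%; this is worth weighing before an endpoint is dropped.

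The cost is a few sentences in the protocol or analysis plan, with no patients and no data. The downsides are simultaneous confidence intervals that are less simple than Bonferroni's and, under the first option, a stricter gate to the low-risk stratum than a per-endpoint hierarchy would give.
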